### 2.2. Study Design

During the Connecting Health and Technology study, participants completed four day mFRs using the CHAT application at baseline and at the end of the 6-month randomised controlled trial. During both visits height and weight data were collected. Participants were asked to capture before and after images of all eating occasions using a mobile device (iPod Touch) provided by the research team. On the initial visit participants were taught how to use the specifically designed dietary assessment method, the CHAT application, uploaded onto the iPod Touch (iOS6). Participants were asked to place a small fiducial marker in the bottom left hand corner of every image to assist in portion size and colour estimation [38]. Details of the mFR CHAT application have been previously described by Kerr *et al.* [39].

Participants were asked to take images over four consecutive days, from Wednesday to Saturday. On completion of the food record, participant’s clarified the contents of images with an Accredited Practising Dietitian, and verified plate waste or if the leftover food or beverage was consumed at a later stage. Each image obtained during the CHAT study contains metadata on the time, date and location it was taken, allowing for the assessment of whether fresh produce were in season at time of consumption. The food images collected during the CHAT study will be used to validate and test the *Healthy and Sustainable Diet Index*.

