For the development of the proposed methodology, participants completed an mFR at baseline (*n =* 247) and repeated this six months later (*n =* 220). A secondary analysis by the Accredited Practising Dietitian who was involved in the original analysis of all food images collected during the CHAT study will take place. A purpose built Microsoft Access database will be developed to assess the contents of images, and the review of each image pair (including a before and after eating image). A minimum of one image pair per day will be required to be considered a valid day. Five indicators of a healthy and sustainable diet will be assessed using the images captured using the mFR. An objective of this study is to determine whether the five selected dietary behaviours can be assessed from image-based food records without interaction with participants. This is therefore a “proof of concept” approach to developing the Index before replication in possible future interventions. A flowchart outlining the design of the proposed study can be seen in Figure 2.

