Each component incorporated into the *Healthy and Sustainable Diet Index*, will be given a weighting used to calculate a final score measuring adherence to a healthy and sustainable diet. For example, typically indices have a maximum score of 100, with a higher score indicating greater adherence to the preferred dietary pattern [23]. Individual components will be given a weighting to reflect consistency with the recommended dietary and sustainable eating outcomes, for example, fruit and vegetable intake may be given a higher weighting as it contributes to both healthy and sustainable eating.

The theoretically driven *Healthy and Sustainable Diet Index* will be internally validated for reliability, content validity and construct validity using 4-days image-based food records collected during a 6-month randomised controlled trial. The baseline data collected during the CHAT study (*n =* 247) will be randomised into thirds using age- and sex-stratified random sample techniques. Two-thirds of the sample will be randomly selected as the derivation cohort and the image-based mFRs of those selected will be used to develop the *Healthy and Sustainable Diet Index* using regression techniques. The remaining one-third of the sample will be used as the validation cohort for the *Healthy and Sustainable Diet Index*. This Index will also be used in the assessment of food images from the 6-month follow up (*n =* 220), and the results compared with baseline.

To assess content validity, components of the *Healthy and Sustainable Diet*
*Index* will be assessed against the Australian Dietary Guidelines [7]. Construct validity will quantitatively assess how well the Index measures conformance to a healthy and sustainable diet.

To determine a total score using the *Healthy and Sustainable Diet Index*, density scores for each component will be calculated. Internal consistency, one form of reliability, will be assessed using Cronbach’s coefficient α. This test has previously been used in the evaluation of the Healthy Eating Index [70] to examine the degree of association between components, to determine if a diet only has one dimension. The relationship between the components of the *Healthy and Sustainable Diet Index* will be assessed using Pearson correlations coefficient. Principle component analysis will be used to assess if there are independent components of the Index. This will measure if there are any significant independent predictors of an overall score.

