## 3. Discussion

The proposed methodologies described in this paper aim to determine if the mobile food record can be used to accurately measure five key indicators of a healthy and sustainable diet. The availability of dietary intake data collected from 4-day mFRs during the CHAT study enables the refinement of the assessment tool and internal validation of a theoretically driven *Healthy and Sustainable Diet Index*. This Index will be tested on a duplicate sample and a longitudinal sample of adults’ 4-day image-based food records to measure content validity, construct validity and reliability.

The *Healthy and Sustainable Diet Index* will be unique in two ways; firstly it will combine the assessment of eating behaviours that influence health outcomes (e.g., EDNP foods and beverages) and dietary behaviours that significantly burden the environment (e.g., ultra-processed foods, food waste). Secondly, it will require the use of image-based food records, which will enable the accurate assessment of dietary behaviours not assessed in traditional forms of dietary assessment (e.g., individually packaged foods).

Using an mFR application to assess the five healthy and sustainable dietary behaviours described in this paper has the potential for further enhancement of the mFR applications capability as a new dietary assessment method. For example, a current fiducial marker probe exists to alert users when the fiducial marker is not located in the image, as described by Ahmad *et al.* [29]. A similar mechanism to ask the user whether food waste detected in the after image was thrown in the rubbish bin, composted, saved for consumption at a later time or other could be incorporated into the mFR application.

Currently there is limited evidence on whether Australian adults have dietary habits consistent with a sustainable diet. Without adequate evidence in this area, appropriate changes to dietary recommendations and nutrition policy are challenging. Results from the Australian Health Survey indicate most Australian’s have eating habits inconsistent with the Dietary Guidelines, contributing to the burden of diet-related diseases in this country [63]. However, to the authors’ knowledge, there is currently no dietary assessment tool or indexing system to assess and monitor whether individuals have dietary behaviours inconsistent with a sustainable diet, such as the use of individual food packaging and plate waste.

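### No planned analysis tests whether the five behaviours can be assessed from images without participant contact: the records were clarified with participants, and image-only coding is never compared with clarified coding

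*Protocol article*

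**What the plan says.** Section 2.2 of the Protocol article gives as an objective to "determine whether the five selected dietary behaviours can be assessed from image-based food records without interaction with participants", and calls the approach a proof of concept. The Discussion (Section 3) goes further: the methods "aim to determine if the mobile food record can be used to accurately measure five key indicators of a healthy and sustainable diet". Section 2.3.5 also says that plate waste will be captured accurately from before and after images.

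On the source data, Section 2.2 says that when the food record was complete, participants "clarified the contents of images with an Accredited Practising Dietitian, and verified plate waste or if the leftover food or beverage was consumed" later. On the coder, it specifies "A secondary analysis by the Accredited Practising Dietitian who was involved in the original analysis of all food images collected during the CHAT study". A new database will be built for review of each image pair.

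Section 2.5 lists the validation. The Index will be "internally validated for reliability, content validity and construct validity using 4-days image-based food records collected during a 6-month randomised controlled trial". For content validity, its components "will be assessed against the Australian Dietary Guidelines". For reliability, "Internal consistency, one form of reliability, will be assessed using" Cronbach's alpha. Pearson correlations between components, principal component analysis, a split into derivation and validation cohorts, and a comparison of six months with baseline complete the list.

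**The concern.** An objective about coding without participant contact needs two things: coding that made no use of such contact, and a reference to judge it against. The article secures neither. Participants had contact with a dietitian on the very items at issue, the coder has prior exposure to the original analysis, and no listed analysis sets image-only values beside clarified ones.

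The study could therefore finish with a scored and internally validated Index and still hold no evidence on whether images alone are enough. That evidence is what would support the use in population monitoring that the Abstract and Introduction promote. The timing also matters. Once this coder has worked through the images with clarified information available, a clean image-only pass by the same coder is no longer possible.

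**Working it through.** The plan gives no figure on this point, so the check sets the objective beside the data source, the coder and each analysis.

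**1. Do the source data involve interaction?** Yes. Section 2.2 records clarification of image contents and verification of plate waste, including the fate of leftovers.

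**2. Is the second coding protected from that information?** The article does not say. The coder is "the Accredited Practising Dietitian who was involved in the original analysis of all food images" from the CHAT study. No masking, independent coder or separate image-only pass is described.

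**3. Does any planned analysis answer the objective?**

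| Planned step (Section 2.5) | What it compares | Image-only against clarified coding? |
|---|---|---|
| Content validity | Index components with the dietary guidelines | No |
| Construct validity | Index with the concept of a healthy and sustainable diet | No |
| Cronbach's alpha, Pearson correlations, principal components | Index components with each other | No |
| Derivation and validation split | One part of the baseline sample with another | No |
| Six months against baseline | Index over time | No |

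Each step can be computed whether or not the coder drew on clarified information.

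**4. Does the answer depend on how the coder works?** There are two cases.
- The coder uses the clarifications. The coding then is not free of interaction, and errors that images alone would cause can stay hidden.
- The coder uses only the images. The coding then is free of interaction, but nothing shows how close it is to the clarified record.

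In both cases the plan yields no estimate of agreement or bias for any of the five indicators.

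**5. Which indicator is most exposed?** Plate waste. Section 2.3.5 scores it as the percentage left in the after-image, and that image cannot show whether the food was eaten later. Section 2.2 relied on the participant to settle this. The Discussion suggests that a future version of the application could ask the user. Packaging is also exposed: Section 2.3.2 concedes that it may be removed before the first image is taken.

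**6. Illustration of size.** Let W be the waste seen in the after-image and f the share of it that is later eaten. True waste is W × (1 − f), so image-only coding overstates waste by the factor 1/(1 − f). The documents give no value for f, so the values below are assumed. The last column applies them to the 30% visible waste in the Section 2.3.5 example.

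| Assumed f | Factor 1/(1 − f) | True waste if 30% is visible |
|---|---|---|
| 10% | 1/0.9 = 1.11 | 30% × 0.9 = 27% |
| 20% | 1/0.8 = 1.25 | 30% × 0.8 = 24% |
| 50% | 1/0.5 = 2.0 | 30% × 0.5 = 15% |

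**The case against.** The best defence is that the article describes an image-based assessment. Section 2.2 speaks of reviewing each image pair, and Section 2.3.5 defines plate waste from the after-image. Whether clarifications are displayed in the database is a detail that a condensed article may leave to the full protocol, and the flow chart in Figure 2 is not available here. The study is also framed as a proof of concept, and it allows for partial failure. Waste can be classed as undeterminable for compostability, the limits on packaging and on the origin of produce are admitted, and Section 2.5 denies a high weight to components that images cannot measure accurately.

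Much of this stands, and it rules out several stronger readings:
- A reader might infer that the coder held the clarification sessions, did the whole original analysis, or met participants face to face. The text says only that the dietitian was involved in that analysis, and it does not state how the clarification took place.
- A reader might infer that the second coding will certainly use the clarifications, or that they would hide image-only error completely. Neither is stated. Complete hiding would require recall or display of every clarification across up to 467 records (247 at baseline plus 220 at six months).
- A reader might infer that the objective can only come out as a success. The fair statement is that no criterion and no comparator are given.
- A reader might ask for visit and trial arm to be masked as well. This objective does not need it.

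The defence does not supply the missing comparison. The article itself fixes the objective, the coder and the validation steps, and these do not fit together. A pure feasibility reading does not rescue the plan either. The only stated category for failure to code concerns compostability, and Sections 2.3.5 and 3 claim accuracy, which needs a reference.

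**Conclusion.** The point holds in this form: the analyses described can neither support nor refute the claim of assessment without interaction or the claim of accurate measurement. This rests on the article's own list of analyses and does not require that the coder will in fact use clarified information. That use remains a possibility against which no safeguard is stated.

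The gap covers all five indicators and is most serious for plate waste. The size of any resulting error is unknown. The factors of 1.11, 1.25 and 2.0 show how the error would scale with f and are not estimates for this study.

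**What to change.** Before coding starts:

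1. Do the second-pass coding from the image pair and date stamp only, with the clarifications and the original coding hidden. Lock the result.
2. Then compare it with clarified coding wherever clarified information was kept. This should cover plate waste at least, since participants verified it. For the other indicators, recode a subsample with the clarifications available. A ready reference should not be assumed for them: Section 3 says that the images have not been used before to measure these behaviours, so clarified coding of packaging or compostable class may not exist.
3. Report per indicator the mean difference and limits of agreement for serves, grams and waste percentage, kappa for categories, and the share of images that could not be coded.
4. State possible recall by the coder as a limitation.

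The cost is a display setting in a database still to be built, a second coding pass on a subsample, and one agreement analysis. No new staff are needed.

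If this cannot be done, restate the objective as coding of previously clarified records, and withdraw the claims of no interaction and of accuracy. That costs only a change of text.

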**Figure 2 nutrients-07-05226-f002:**
[figure not shown]
Flow chart of study design.

### 2.3. Assessment of Healthy and Sustainable Dietary Behaviours

For the development of a *Healthy and Sustainable Diet Index*, dietary behaviours were identified from evidence of their supportive or unsupportive role within a healthy and/or a sustainable diet and the inclusion of details that can be assessed using images. Descriptions of each component’s role within the context of a healthy and sustainable diet are outlined below. The five indicators to be assessed using the mFR application include: the intake of ultra-processed EDNP foods and beverages, individually packaged foods and beverages, fruit and vegetables (including seasonality), dairy, eggs and meat portions, and plate waste. These dietary behaviours will be assessed using the following proposed methodologies.

#### 2.3.1. Ultra-Processed EDNP Foods and Beverages

Processed foods form a large component of modern diets and have been linked to the growing rates of overweight and obesity [7,40,41,42]. A definition of food processing is “all methods and techniques used by industry to turn whole fresh foods into food products” [43]. Food processing is important to ensure an adequate and safe food supply [44], however, high levels of food processing often increases the energy density of food due to “ultra-processing” with the addition of added fat and sugar. In general, foods that have been highly or ultra-processed are more likely to contain high levels of saturated fats, added sugars and/or sodium and minimal levels of micronutrients therefore are often categorised as “energy-dense nutrient-poor” choices [41,45]. Energy-dense nutrient-poor foods and beverages are associated with poor diet quality, overweight, obesity and chronic disease [45,46], as well as being some of the most emissions-intensive food products due to the processing, packaging and landfill necessary to produce these foods in certain locations [9]. Although all EDNP foods may not negatively affect the environment more than other food items, these foods are generally low in nutrients [7]. In addition, the excessive intake of kilojoules above an individual’s energy requirements, from these EDNP foods and beverages, is a dietary behaviour unsupportive of health whilst creating unnecessarily burden on natural resources [7,15]. Highly processed takeaway foods and poor diet quality are associated with abdominal obesity in young adults [40,47] and compared to older age groups, young adults are more likely to consume EDNP that are convenient, highly processed and packaged, such as meat pies, fried potatoes, pizzas, crisps, confectionary, savoury pastries, chocolate and sugar-sweetened beverages [40,48]. Hence, processed food is not the issue in a healthy and sustainable diet, the issue is EDNP ultra-processed foods.

Ultra-processed foods are defined as those that require minimal, if not any, culinary preparation [41]. Previous studies have relied on household expenditure surveys and semi-quantitative food frequency questionnaires to assess the intake of ultra-processed foods [41,42,43], yet no studies have investigated the consumption of ultra-processed foods in Australia. A unique aspect of the methods to be used is that EDNP ultra-processed foods will be assessed using image-based mFRs. For inclusion in this component only ultra-processed foods and beverages categorised as energy-dense and nutrient-poor, such as cakes, crisps, commercial burgers and sugar-sweetened beverages will be used [7]. Ultra-processed EDNP foods and beverages will be assessed according to the Australian Dietary Guidelines serve sizes-one serve of EDNP food or beverage being equivalent to 600 kJ (143 kcal) [7]. Nutrient dense foods that are highly processed, such as bread, will be excluded due to associated health benefits.

An example image of ultra-processed EDNP foods collected using the mFR application can be seen in Figure 3. Using the proposed assessment protocol, this eating occasion would be recorded as 14 serves of ultra-processed EDNP foods. The two pieces of fried chicken appearing in the after eating image would not be counted as ultra-processed EDNP serves but rather non-compostable food waste.

We can appreciate all EDNP foods may not necessarily be worse for the environment than other food items, however, in regard to health consequences, these food items offer minimal, if any, nutritional benefit. In addition, the excessive intake of kilojoules above an individual’s energy requirements, from these EDNP foods and beverages, is a dietary behaviour unsupportive of health whilst creating unnecessarily burden on natural resources.

**Figure 3 nutrients-07-05226-f003:**
[figure not shown]
Example of using an mobile food record (mFR) to assess ultra-processed energy-dense nutrient-poor foods. (**a**) Before eating image; (**b**) After eating image shows the food waste. The number of energy-dense nutrient-poor food and beverage (EDNP) serves consumed were: 1 sausage roll (commercial, 175 g) = 2100 kJ, fried sausage (large) 1300 kJ × 2 = 2600 kJ, crumbed fried sausage (large) 1800 kJ × 2 = 3600 kJ → Total: 8300 kJ/600 kJ = 14 serves of EDNP foods.

#### 2.3.2. Individually Packaged Foods and Beverages

Food packaging plays a crucial role in maintaining a safe food supply and has the ability to reduce waste by retaining the effect of food processing to extend shelf life [49]. However, food packaging negatively impacts the environment at a number of stages including during production, transport and land fill [15]. Individually packaged foods are convenient and are becoming more common in Australian supermarkets. An Australian study assessed attitudes towards environmentally friendly eating behaviours and found people believe food packaging has a greater impact on the environment compared to the consumption of meat [50].

Key messages in Appendix G of the Australian Dietary Guidelines encourage people to select foods with appropriate packaging and recycle due to the impact on natural resources [7]. Food packaging is not assessed by traditional dietary assessment methods. Images from mFRs show great potential for the accurate assessment of the intake of individually packaged products as they are easily identifiable from the before eating images. Due to the negative impact of packaging on the environment, all individually packaged items will be recorded regardless of the nutrient composition of the food it originally contained. However, individually packaged foods, classified as either EDNP or healthy, will be counted separately to allow for further assessment of adherence to a healthy and sustainable diet. Foods and beverages served from larger packages (so not individually packaged) such as a glass of milk poured from a two litre bottle will not be recorded due to the unavoidable use of larger packages to ensure a safe food supply. A limitation of this method is that some food or beverages may be removed from individual packaging prior to the before eating image being taken. This challenge could be avoided by requesting participants do not remove individual packaging prior to taking images using the mFR.

An example of an image containing individually packaged items collected using the mFR application can be seen in Figure 4. Using the proposed protocol, this eating occasion would likely be assessed as containing two individually packaged EDNP food items and one individually packaged EDNP beverage item.

